### Secondary outcome

The secondary outcomes will be to evaluate the fruit and vegetable intake of women and children, post-harvest practices among farmers, traders, and women, food waste behaviour of women, BMI-for-age in women and children, the knowledge level of women regarding fruits and vegetables, and the impact of these on nutritional outcomes (Table 2).

**Table 2 tab2:** Table of primary and secondary outcomes.

Outcome type	Outcome	Measurement method	Assessment time points
Primary	Anaemia status in women and children	Haemoglobin testing (Hemocue 501 meter)	Baseline and post-intervention
Primary	Dietary Diversity Score (DDS)	24-h dietary recall and food group classification	Baseline and post-intervention
Secondary	Household food waste behaviour	Structured food waste behaviour questionnaire	Baseline and post-intervention
Secondary	Fruit and vegetable intake	Food Frequency Questionnaire (FFQ)	Baseline and post-intervention
Primary	Post-harvest handling knowledge/practices	Survey and Focus Group Discussion	Baseline
Primary	Anthropometric measurements (BMI, z-scores)	Height, weight using WHO protocol	Baseline and post-intervention

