### Statistical analysis

Statistical package for social sciences (SPSS) (IBM Corp. Released 2022. IBM SPSS Statistics for Windows, Version 30.0. Armonk, NY: IBM Corp) will be used for the data analysis. The Kolmogorov-Smirnov and Shapiro-Wilk tests will be used to assess the normality of the quantitative data. A *p*-value less than 0.05 indicates that the data is not normally distributed, and vice versa. The characteristics of the study participants will be analysed using descriptive statistics. A chi-square test will be done to assess the relationship between categorical variables. Fisher’s exact test will be employed to determine the significance level. Parametric tests will be used to analyse normally distributed data, and non-parametric tests will be used to analyse data that is not normally distributed. Parametric tests will be presented in terms of mean and standard deviation, and non-parametric tests will be presented in terms of median (maximum-minimum). A t-test will be conducted to compare the mean differences of the outcomes of interest within and between study groups at baseline and post-intervention. Regression analysis will be conducted to predict the drivers of fruit and vegetable loss, adjusting for age and gender. Partial correlation will be used to assess the strength of association among the variables. All *p*-values will be significant at *p* < 0.05.

The primary analysis will follow the intention-to-treat (ITT) principle, including all participants as initially allocated, regardless of their adherence to the intervention protocol. This approach ensures an unbiased estimate of the intervention effect. For secondary per-protocol analyses, only participants who fully adhered to the intervention will be considered. To address missing data, particularly in outcome measures such as dietary assessments and anthropometry, multiple imputation methods will be employed under the assumption that data are missing at random. Sensitivity analyses will be conducted to assess the robustness of results. This strategy helps maintain the validity and reliability of findings despite potential data gaps.

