To account for multiplicity in the analysis of primary and secondary outcomes, the study will employ a structured analytical approach. Primary and secondary outcomes will be pre-specified to avoid *post hoc* comparisons. Where outcomes are assessed at multiple time points (e.g., baseline and post-intervention), repeated-measures analysis or appropriate statistical corrections such as the Bonferroni adjustment will be applied to control the risk of Type I error. Subgroup analyses (e.g., by community or demographic characteristics) will be exploratory and clearly labelled as such to prevent overinterpretation. These steps ensure robust and reliable interpretation of findings while maintaining the statistical integrity of the study. This protocol was developed in consultation with a statistician. The statistician reviewed sample size estimations and the statistical analysis plan to ensure methodological soundness. This is reflected in the detailed statistical analysis section, which outlines methods for dealing with missing data, baseline comparability, and outcome estimation.

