### Adverse events

Potential challenges anticipated in the study include participant dropout, seasonal variations in fruit and vegetable availability, and possible contamination between intervention and control communities. The study incorporates regular monitoring, community engagement, and logistical planning to mitigate these risks. Additionally, potential discomfort during haemoglobin testing has been noted, with mitigation through trained phlebotomists and standard operating procedures.

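### The protocol does not fix one between-group effect estimate that uses the baseline value; it lists within- and between-group tests, with normality tests choosing the method

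*Protocol article*

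**What the plan says.** The protocol article, Statistical analysis, states that a t-test will compare mean differences in the outcomes "within and between study groups at baseline and post-intervention". Kolmogorov-Smirnov and Shapiro-Wilk tests at p < 0.05 classify each quantitative variable, and then "Parametric tests will be used to analyse normally distributed data, and non-parametric tests will be used to analyse data that is not normally distributed". The only covariate adjustment named belongs to a different question: "Regression analysis will be conducted to predict the drivers of fruit and vegetable loss, adjusting for age and gender".

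For outcomes measured at more than one time, the same section says that "repeated-measures analysis or appropriate statistical corrections such as the Bonferroni adjustment will be applied to control the risk of Type I error". No group-by-time term or other contrast is named. The section also claims to cover baseline comparability, but gives no method for it.

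Table 2 (Secondary outcome section) gives the time points as "Baseline and post-intervention" for anaemia status, dietary diversity, anthropometry, waste behaviour, and fruit and vegetable intake. Post-harvest handling knowledge and practices, labelled primary, is measured at baseline only. Study design and Study duration place a six-month intervention between the two assessments. The Adverse events section lists "seasonal variations in fruit and vegetable availability" among the anticipated challenges.

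**The concern.** At least four results could each claim to be the planned effect analysis: a post-intervention comparison, a comparison of changes, a pair of within-arm tests, and a repeated-measures analysis. They estimate different things and need not agree.

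- **Within-arm tests.** They measure the intervention plus whatever else changed over six months, including produce supply. If one arm crosses p < 0.05 and the other does not, that pattern can be taken for an effect when none exists.
- **Post-only test.** It carries part of any baseline difference between arms into the estimate and does not use the precision that the baseline offers.
- **Normality switch.** It makes the quantity estimated (difference in means or rank comparison) depend on the data, so outcomes may be reported on different scales. The plan attaches no adjusted effect size to the rank branch.

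**Working it through.** The protocol gives no figure on this point to reproduce, and the check does not depend on how the 70 per group was reached. Clustering is ignored throughout.

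**Inputs**
- From Sample size calculation: 70 households per group and 10% non-response, so 70 × 0.9 = 63 per arm. Power is 80% and the significance level 5% (two-sided assumed).
- Assumed, because the protocol gives neither: correlation r between baseline and post-intervention values of 0.3, 0.5 or 0.7; seasonal shift of 0.2-0.3 SD, equal in both arms.
- Assumed for illustration: a baseline difference between arms of 0.3 SD.

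**1. Within-arm tests with no intervention effect.** The paired test has noncentrality shift × √63 / √(2(1 − r)), with 62 degrees of freedom. Let p be the probability that one arm shows significant improvement. The pattern of significance in intervention but not in control then has probability p(1 − p).

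| r | shift (SD) | p | p(1 − p) |
|---|---|---|---|
| 0.5 | 0.2 | 0.346 | 0.226 |
| 0.5 | 0.25 | 0.497 | 0.250 |
| 0.5 | 0.3 | 0.650 | 0.228 |
| 0.7 | 0.2 | 0.523 | 0.249 |
| 0.7 | 0.25 | 0.713 | 0.205 |
| 0.7 | 0.3 | 0.857 | 0.123 |

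The range is 12-25%. At r = 0.3 it is 19-25%.

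**2. Precision.** Relative to a post-only comparison (variance factor 1), the change score has factor 2(1 − r) and baseline adjustment has 1 − r². The detectable difference is (1.96 + 0.842) × √(2 × factor / 63).

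| r | change factor | adjusted factor | post-only | change | adjusted |
|---|---|---|---|---|---|
| 0.3 | 1.40 | 0.91 | 0.50 SD | 0.59 SD | 0.48 SD |
| 0.5 | 1.00 | 0.75 | 0.50 SD | 0.50 SD | 0.43 SD |
| 0.7 | 0.60 | 0.51 | 0.50 SD | 0.39 SD | 0.36 SD |

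Adjustment cuts residual variance by 9%, 25% and 49%. A change score is worse than a post-only test at r = 0.3, so it matters which of the two the t-test sentence means.

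**3. Baseline difference carried forward.** A post-only contrast keeps r × 0.3 SD: 0.15 SD at r = 0.5 and 0.21 SD at r = 0.7 (0.09 SD at r = 0.3). Conditional on that difference, the type I error of a nominal 5% test is 10% at r = 0.5 and 14% at r = 0.7. A change score errs the other way, by −(1 − r) × 0.3: −0.15 SD and −0.09 SD.

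**4. Normality switch.** In simulation at n = 63, Shapiro-Wilk rejected a bell-shaped integer score from 0 to 10 in about 95% of samples (rounded normal, mean 5, SD 1.5) and about 48% (same, SD 2). Discreteness alone could thus send dietary diversity, a primary outcome, to a rank test.

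**The case against.** **The baseline is not ignored altogether.** A reader might infer from the t-test sentence that the plan contains no baseline adjustment at all. The text does not support that. Repeated-measures analysis is offered, its group-by-time term would use the baseline, and the mean differences compared between groups can be read as changes. This stands. But a Bonferroni correction would satisfy the same sentence and uses no baseline information, so the plan can be carried out in full without a contrast that uses it.

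**Covariates are commonly left to an analysis plan that is not shown.** True, and a missing covariate list is not the point. The protocol states an effect analysis, and what it states is open and partly unsuitable.

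**Season is shared by both arms.** A reader might infer that season also spoils the between-group comparison. A common shift cancels there; only the within-arm tests are affected. Nothing in the protocol shows that the arms are visited at different times. Nor does it say that an effect will be declared because only one arm reaches significance; the 12-25% is the risk if results are read that way. Doubling it would count the pattern in control only, which is not the misreading at issue.

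**Random allocation makes the post-only contrast unbiased on average.** Correct. The 0.15-0.21 SD is conditional on an assumed imbalance. With two communities per arm, averaging over allocations gives little protection in the one trial run.

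**Coverage is incomplete.** Anaemia status is categorical, so the t-test and the switch do not govern it. No model can show an effect on the outcome measured at baseline only. Both points stand.

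**Conclusion.** The point holds in a limited form: the protocol does not commit to one between-group contrast that uses the baseline, and the tests it lists leave both the estimate and its scale open. The within-arm tests and the normality switch are the parts stated badly in the text itself.

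The size rests on assumed correlations, seasonal shift and baseline imbalance. Dietary diversity comes from a single 24-hour recall, so the low end of the correlation range, with a 9% gain, should be taken seriously. The variance reductions are upper bounds: adjusting for individual baselines does not remove community-level variance and does not cure having two communities per arm. The carried-forward difference treats the imbalance as chance variation between individuals. The change should be made because it is free and removes ambiguity, even if the gain in precision proves small.

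**What to change.** 1. For each continuous outcome measured at both times (haemoglobin, dietary diversity score, BMI and z-scores, waste-behaviour scores), define the effect estimate as the arm coefficient, with 95% CI, from one model of the post-intervention value on arm and the same outcome's baseline value. Handle community as in the rest of the analysis.
2. For anaemia status, use the logistic analogue with baseline status as covariate.
3. Fit these models whatever the normality tests show. Check residuals, and use a transformation or bootstrap if needed.
4. Report within-arm changes descriptively, without tests.
5. State that repeated-measures analysis and Bonferroni correction are not substitutes for this contrast.

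The cost is wording in the analysis section. The model uses only assessments already planned at both times. The Study status and timeline section says that analysis starts after data collection and that no results have been generated, so the change can still be made before any result is seen.

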## Outcomes

### Primary outcome

The primary outcome is to assess the impact of post-harvest loss of fruits and vegetables on the nutritional status of women and children.

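### Table 2 and the text disagree on which outcomes are primary, and the multiplicity rule addresses time points without controlling error across the several primary outcomes

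*Protocol article*

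**What the plan says.** The protocol article describes what is primary in three places.

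- The Primary outcome section gives an aim, not a variable: "The primary outcome is to assess the impact of post-harvest loss of fruits and vegetables on the nutritional status of women and children".
- Table 2 marks four rows as primary: "Anaemia status in women and children"; the dietary diversity score; post-harvest handling knowledge/practices, for which baseline is the only assessment time point; and the row that begins "Anthropometric measurements (BMI, z-scores". The other three primary rows are assessed at baseline and after the intervention.
- The text of the Secondary outcome section, directly above Table 2, lists as secondary the post-harvest practices of farmers, traders and women, and also "BMI-for-age in women and children".

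The Statistical analysis section sets one threshold: "All *p*-values will be significant at *p* < 0.05". It plans t-tests both within and between groups, at baseline and after the intervention. Its multiplicity paragraph opens "To account for multiplicity in the analysis of primary and secondary outcomes, the study will employ a structured analytical approach". It promises pre-specified outcomes and labels subgroup analyses exploratory. The one correction it names is this: "Where outcomes are assessed at multiple time points (e.g., baseline and post-intervention), repeated-measures analysis or appropriate statistical corrections such as the Bonferroni adjustment". The article does not split the significance level across outcomes, put the outcomes in order, or require all primary outcomes to succeed.

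**The concern.** Post-harvest practices are primary in the table and secondary in the text, and so is BMI-based anthropometry. A result on either could later be reported under either label. The practices row cannot test the intervention at all as listed, because it has no post-intervention assessment.

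The multiplicity paragraph states the right problem, several outcomes, and then names a remedy for a different one, several visits. The remedy is also optional, since repeated-measures analysis may be used in its place. That leaves several primary outcomes, each tested at 0.05, and no rule for what counts as a positive trial. At stake is whether a significant primary result can be read as evidence at the 5% level.

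**Working it through.** **Step 1. Status of each outcome, side by side.**

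| Outcome | Primary outcome section | Table 2 | Secondary outcome text |
|---|---|---|---|
| Anaemia, women and children | not named; fits nutritional status | primary | not listed |
| Dietary diversity score | not named | primary | not listed |
| Post-harvest knowledge/practices | not named | primary, baseline only | practices listed as secondary |
| Anthropometry (BMI, z-scores) | not named; fits nutritional status | primary | BMI-for-age listed as secondary |

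The direct contradictions are in the last two rows.

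**Step 2. Number of primary tests that can compare arms after the intervention.**

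- Anaemia: women and children, 2.
- Dietary diversity: the Dietary diversity score section defines it separately for women and children, 2.
- Women's BMI: 1.
- Child z-scores: the Anthropometric measurements section names weight-for-height, weight-for-age and height-for-age, 3.
- Knowledge/practices: baseline only, 0.

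Total: 2 + 2 + 1 + 3 = 8.

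**Step 3. Family-wise error with no correction across outcomes.** The article states no such figure, so there is none to reproduce. Its household sample size uses a single 5% level. With k independent tests at 0.05 and no true effect, the chance of at least one significant result is 1 − 0.95^k. Correlations between the outcomes are not given, so they are assumed. The correlated figures come from simulating k equally correlated two-sided z-tests (400,000 draws).

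| Tests counted | Independent | Correlation 0.3 | Correlation 0.5 | Correlation 0.7 |
|---|---|---|---|---|
| 8 (Step 2) | 1 − 0.95^8 = 33.7% | 29.9% | 25.0% | 19.1% |
| 4 (each primary row as one test) | 1 − 0.95^4 = 18.5% | 17.4% | 15.6% | 13.1% |
| 3 (as above, without the baseline-only row) | 1 − 0.95^3 = 14.3% | 13.7% | 12.5% | 10.9% |

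**Step 4. Would the stated correction be enough?** Suppose Bonferroni for two time points were applied to every outcome, so each test is at 0.05/2 = 0.025. Eight independent tests then give 1 − 0.975^8 = 18.3%. Error across outcomes is still well above 5%.

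**Step 5. Power if several outcomes stay primary.** A two-sided test with 80% power at 0.05 has an expected z of 1.960 + 0.842 = 2.802. The strictest Holm step with eight tests uses 0.05/8 = 0.00625, critical value 2.734. Power there is Φ(2.802 − 2.734) ≈ 53%. Restoring 80% needs (2.734 + 0.842)² / 2.802² ≈ 1.63 times the sample size. With four tests, at 0.05/4 = 0.0125, power is about 62% and the ratio about 1.42.

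**The case against.** The other side has several fair points.

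- A reader might count nine primary tests and quote 27% to 37%. The ninth would be the knowledge/practices row, which is baseline-only and cannot compare arms after the intervention. Replacing it with the BMI-for-age z-score brings in an item that the text calls secondary. Eight is the count the article supports.
- Independence is an upper case. The three child z-scores share the same child's weight and height, so the true figure is below 34%. The article also does not say that one significant primary result is enough. Any single percentage is therefore conditional.
- A reader might infer three mutually incompatible definitions of the primary outcome. The Primary outcome section is vague, but nutritional status is compatible with the anaemia and anthropometry rows, and the association it describes is also the stated primary objective. The flat contradiction is between Table 2 and the text, for two items.
- A reader might say that a correction for time points is pointless because baseline plus one follow-up gives one effect per outcome. As written, the plan runs within- and between-group t-tests at both visits, so there are several tests per outcome. The sentence should not be deleted without changing that.
- The divisor for an adjustment could be left to a separate analysis plan, and the time-point sentence does touch every primary outcome measured twice.

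These points narrow the size of the problem. They do not remove it. An analysis plan could supply a divisor, but it could not decide which of two published labels governs without contradicting one of them. The paragraph that claims to cover multiple outcomes names no correction across them.

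**Conclusion.** The point holds in this form. Two items carry opposite labels, one primary row cannot test the intervention, the Primary outcome section names no variable, and type I error across the primary outcomes is not controlled.

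The size is conditional on no true effect on any outcome, success on any one significant primary test, and no correction across outcomes. On eight tests, family-wise error is then about 34% if independent and about 25% at an assumed correlation of 0.5. Counting the four rows as single tests gives about 16% to 19%. Every count shown exceeds twice the nominal 5%. The figures also assume that each individual test truly holds 5%; with four randomised communities that is a separate question. The article does not show that the investigators intend to claim success on whichever test is significant, only that nothing in it prevents this.

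**What to change.** Before any analysis by arm:

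1. Give each outcome one status, so that Table 2, the Primary outcome section and the Secondary outcome text agree, and name the variables.
2. Remove the baseline-only knowledge/practices row from the primary outcomes of the arm comparison.
3. Either name one primary outcome for the post-intervention arm comparison, chosen from those already measured at both visits, or keep several and apply Holm across all of them.
4. Replace the time-point Bonferroni sentence with that rule. State that the effect test is one between-arm post-intervention comparison per outcome, and that within-group and baseline tests are descriptive only.
5. Document this as a protocol amendment made without sight of results by arm, as the Protocol amendments section requires for changes to outcomes or analysis. The Study status and timeline section says that no results had been generated or analysed at submission; the amendment must confirm that this is still so for results by arm.

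The cost is wording and an amendment, with no new data. The downside is fewer primary results that can be claimed. If several outcomes stay primary, power at the strictest Holm step is also lower: about 53% with eight tests for a test planned at 80%. A single primary outcome avoids that loss.

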### Consent and participation

The trial will strictly adhere to the World Medical Association Declaration of Helsinki. The researchers will explain the purpose of the study, procedures, benefits, withdrawal options, confidentiality, and voluntary participation to participants and their guardians in a language they understand. Farmers, traders, women, and their children can participate in the study only after giving consent and assent, and their guardian must also provide consent by signing or thumbprinting the informed consent form.

### Adherence strategies and monitoring procedures

To ensure effective implementation of the intervention, this study will employ multiple strategies to improve adherence and monitor compliance. These include regular follow-up through bi-weekly phone calls and monthly home visits, simplified educational materials in local languages, non-monetary incentives such as recognition certificates, and participant feedback mechanisms to enhance engagement. Monitoring adherence will involve tracking attendance at educational sessions, conducting home visit assessments of storage practices, collecting monthly self-reports, and performing periodic dietary and anthropometric evaluations. These combined strategies aim to foster consistent participation, reinforce learning, and ensure reliable measurement of the intervention’s impact on nutritional outcomes.

